### Recruitment

Participants will be recruited through email invitations sent to Coventry University Faculties and social media (Twitter, Facebook). Professional social media accounts will be created according to the British Psychological Society guidelines [28]. Recruitment from NHS facilities (primary and secondary care) will require the clinical care team to screen potential participants, and if participants consent to be contacted, the researchers will contact the participant.

### Study assessments

During the first visit, participants will undergo screening to ensure they meet the study inclusion/exclusion criteria. Participants will be given an opportunity to ask questions to ensure they understand all procedures of the study, and a written informed consent will be taken afterwards. Participants will be informed that they are able to withdraw from the study at any point. If a participant becomes ineligible during the study period, they will be withdrawn from the study.

#### Blood sample

Blood samples will be collected by a phlebotomy-trained member of the research team according to Good Clinical Practice (GCP). Blood samples will be analysed for cardiac and inflammatory biomarkers: cardiac troponin T (cTnT); N-terminal pro B-type natriuretic peptide (NT-proBNP); tumour necrosis factor alpha (TNFα); interleukins 1β, 6 and 10; C-reactive protein (CRP), d-dimer and vascular endothelial growth factors (VEGFs). In addition, microRNA expression profiles will be assessed (TaqMan™ Array Human MicroRNA A Cards, Applied Biosystems, USA).

#### Cardiorespiratory fitness

A medical history, physical examination and 12-lead electrocardiogram coupled with heart rate variability will be performed prior to a maximal cardiopulmonary exercise test. The test will include a ramped exercise protocol using an electronically braked semi-recumbent cycle ergometer (Ergoselect 600, Germany) and gas exchange monitoring (Ultima Series, Medgraphics, UK) to measure peak oxygen consumption (VO_2peak_) and lung volumes. A maximal ramp test will be undertaken with the workload starting at 0 W. Pedal frequency will be maintained at 60–70 revolutions per minute. Participants will be verbally motivated during the tests according to an agreed template to ensure uniformity across all tests. Participants perceived exertion will be monitored using the BORG scale. The test will be terminated if participants’ reach peak exertion (i.e. RER > 1.1), the participant requests to stop before the exercise protocol completion or any indication for exercise termination described in the ATS/ACCP statement on cardiopulmonary exercise testing [29].

#### Cardiovascular function

Cardiac and vascular parameters will be assessed at rest and peak cardiopulmonary exercise using non-invasive methods (Starling SV – Baxter Healthcare Ltd., USA) and echocardiogram. An echocardiogram will be performed using ultrasound to acquire 2D real-time images of the heart to assess cardiac structure and function (Vivid IQ, GE Healthcare, USA). Participants will be asked to undress to the waist, and gowns will be offered to all participants. An ultrasound probe will be placed on the chest with lubricating gel to form good contact between the probe and skin for image acquisition. Echocardiography will be performed at rest and at peak exercise.

Arterial stiffness, a measure of arterial function, will be assessed at rest using non-invasive gold standard techniques which allows for both pulse wave analysis (PWA) and pulse wave velocity (PWV)measurements (Sphygmacor device; AtCor Medical, NSW, Australia). A blood pressure cuff will be placed on the participants’ upper left arm for PWA assessment. For PWV assessment, a tonometer will be placed against the neck and a blood pressure cuff will be placed on the upper thigh to simultaneously measure carotid artery pulse wave velocity and femoral artery blood pressure.

#### Questionnaires

Participants will be asked to complete four questionnaires to assess quality of life, fatigue, depression, anxiety, stress and sleep quality during both visits. Questionnaires include Short Form 36 (SF-36); Chalder Fatigue Scale; Depression, Anxiety and Stress Scale-21 (DASS-21); and Pittsburgh Sleep Quality Index (PSQI). Questionnaires will be checked to ensure completeness of data.

#### Step count, daily activity and sleep

Participants will be provided with a pedometer (Omron Walking Style IV, Japan) to record the daily step count throughout the duration of the study. Step count logs will be completed with daily steps recorded. Physical activity and sleep will be measured over 7 days using an accelerometer worn on the wrist (ActTrust and ActTrust 2, Condor Instruments, Brazil) during the baseline week and the week preceding the end of the intervention.

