## Methods

### Study design, setting and ethics

The present single-centre, prospective, observational and interventional, randomised controlled study will be undertaken at the Coventry University Cardiovascular Research Laboratory between January 2022 and August 2023.

Ethical approval was granted by the Coventry University Research Ethics Committee (P125303) and the UK Health Research Authority National Health Service East Midlands – Leicester South Research Ethics Committee (22/EM/0090). The study will be conducted in accordance with the Declaration of Helsinki. The study was prospectively registered on ClinicalTrials.gov (NCT05492552) on 7 April 2022. The participant timeline is shown in Fig. 1.

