### Intervention

#### Physical activity intervention group

The exercise intervention group will undergo a 12-week home-based physical activity intervention. The participants will be asked to increase their daily steps by at least 2000 steps per day from baseline, e.g. walking for approximately 30 min in addition to baseline, 5 days a week. A large cohort study of 9306 participants demonstrated that an incremental increase in physical activity of 2000 steps per day reduced the risk of cardiovascular events by 10% [30]. A pedometer will be provided to all participants with a diary sheet to record the number of steps per day. Weekly telephone calls lasting 10–15 min each will be made to each participant in the intervention group to provide an opportunity for the participants to ask any questions and for the research staff to encourage the participant to achieve their step goal. Suitable days and times will be arranged for phone calls to take place. After the intervention period, i.e. 13 weeks from the date of the initial visit, participants will be invited to visit the laboratory for follow-up assessments. One week will be allowed for the participants to record their baseline step count. On the first day of the second week, researchers will contact the participant to inform them of which group they have been allocated to. The same outcomes will be measured during the follow-up visit to determine a value of change.

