### Outcome measures

The primary outcome measure is mean change in left ventricular global longitudinal strain after 12 weeks of the study intervention. Secondary outcomes are mean changes from baseline to the end of the intervention period in arterial stiffness (pulse wave velocity and augmentation index), measures of systolic and diastolic function of the heart (i.e. left ventricular ejection fraction, cardiac output, stroke volume, cardiac power, early-to-late filing ratio, right ventricular global longitudinal strain, left atrial strain, ventricular-arterial coupling, right ventricular diastolic function), heart rate variability, functional capacity, lung function, inflammatory and cardiac biomarkers, quality of life and well-being (depression, anxiety, stress, fatigue and sleep measures). Sleep measures include bedtime (h:min), wake-up time (h:min), time-in-bed (h), total sleep time (h), sleep onset latency (min), sleep efficiency (%), number of awakenings and wake after sleep onset (WASO, min), number and timing of naps, inter-daily variability and stability (as markers of circadian rhythmicity), and timing and nature of light exposure during a 24-h period. Additionally, we will assess the differences in the COVID-19 group vs. the non-COVID-19 group.

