### Data analysis methods

Initially, intention-to-treat analysis will be used, and all data will be used from all participants according to the groups to which they have been assigned to. Secondary analysis will involve per-protocol analysis, which will analyse the adherence to the intervention. All obtained data will be used for the analysis. To minimise missing data, participants will be contacted weekly by the research team if in the intervention group and call to all control participants for their follow-up visit as a reminder. As the study requires a single follow-up visit, only complete cases will be analysed, and no data imputation will be used. All statistical analyses will be carried out using the IBM SPSS software, version 28. Descriptive statistics will be presented as means and standard deviations (SD). All data will be assessed for normality using the Kolmogorov–Smirnov test. Independent samples *T*-test or Mann–Whitney *U*-test, as appropriate, will be used to assess the differences in variables between COVID and non-COVID groups. Paired-samples *T*-test or Wilcoxon signed-rank test, as appropriate, will be used to evaluate the differences in variables pre- and post-intervention. Pearson’s or Spearman’s tests (as appropriate) will be used to determine correlation coefficient (*r*). A *p*-value of < 0.05 will be considered statistically significant.

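### Sleep-timing, circadian and light-exposure outcomes are recorded about 12 weeks apart and tested without covariates, so seasonal change in daylight can bias the pre-post tests and the COVID versus non-COVID contrast

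*Protocol article*

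**What the plan says.** - **Recording.** Under Step count, daily activity and sleep: "Physical activity and sleep will be measured over 7 days using an accelerometer worn on the wrist", "during the baseline week and the week preceding the end of the intervention".
- **Spacing.** Under Physical activity intervention group, follow-up is "i.e. 13 weeks from the date of the initial visit", and the first of those weeks is the baseline week ("One week will be allowed for the participants to record their baseline step count").
- **Calendar.** Study design, setting and ethics places the study at one UK site "between January 2022 and August 2023", so participants can start in any season.
- **Outcomes.** Outcome measures lists changes in bedtime, wake-up time, other sleep measures, markers of circadian rhythmicity and the "timing and nature of light exposure during a 24-h period" as secondary outcomes. It adds a comparison of the COVID-19 and non-COVID-19 groups.
- **Analysis.** Data analysis methods names independent-samples t or Mann–Whitney tests for COVID versus non-COVID. The paired t or Wilcoxon test "will be used to evaluate the differences in variables pre- and post-intervention". No covariate is named, and no test is named for comparing the two randomised arms.
- **Balance over the calendar.** The Randomisation section describes no stratification by date. The Recruitment section does not require the COVID and non-COVID groups to be recruited in the same months.

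**The concern.** Two weeks about a quarter of a year apart usually fall in different seasons. Light exposure depends directly on daylight, and bedtime, wake-up time and circadian markers plausibly do too. A paired test in one arm cannot separate a programme effect from the average seasonal shift in that arm. In the non-randomised COVID contrast, a difference in recruitment months would look like an effect of infection. At stake are the conclusions on these secondary outcomes.

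**Working it through.** The document gives no figure for daylight or for the variability of these outcomes, so there is no figure of its own to reproduce. The check has four steps.

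**1. Gap between the weeks.** The baseline week is days 0 to 6. Follow-up is at 13 × 7 = 91 days, so the week before it is days 84 to 90 and the starts are 84 days apart. A looser reading, one week earlier, gives 77 days.

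**2. Change in day length.** Latitude is not in the document; 52.4 N is assumed, with a range of 50 to 55 N. Day length comes from a standard astronomical model (sun 0.833 degrees below the horizon), averaged over each 7-day week. Change = later week minus baseline week, taken over every start date. At 52.4 N and 84 days:

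| Starts spread evenly over | Mean (h) | SD (h) |
|---|---|---|
| A full year | 0.0 | 4.1 |
| Jan 2022 to Jun 2023 | +1.0 | 4.0 |
| Apr 2022 to Jun 2023 | +0.05 | 3.9 |
| Apr to Dec 2022 | −1.8 | 3.3 |
| Jul to Sep | −5.1 | 0.4 |
| Jan to Mar | +5.1 | 0.5 |

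Over a full year the extremes are −5.5 and +5.6 h. For the three spreads of at least a year, over 50 to 55 N and 77 or 84 days, the SD runs from 3.3 to 4.6 h. Concentrated enrolment exchanges spread for a mean shift.

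**3. Noise in a between-arm comparison.** Let an outcome's change move by *b* residual SDs per hour of daylight. The document gives no *b*; 0.05, 0.1 and 0.2 are assumptions. The share of change-score variance due to daylight is (4.1*b*)² / (1 + (4.1*b*)²):

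- *b* = 0.05: 0.042 / 1.042 = 4%
- *b* = 0.1: 0.168 / 1.168 = 14%
- *b* = 0.2: 0.672 / 1.672 = 40%

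With 40 per arm and about 20% attrition (Sample size section), 40 × 0.8 = 32 complete per arm. The chance difference between arms in mean daylight change has a standard error of 4.1 × √(2/32) = 1.03 h.

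**4. Bias in the paired test.** With no true effect, mean daylight change *m* and SD *s*, the paired t statistic has noncentrality *b·m*·√*n* / √(1 + (*b·s*)²). For *n* = 32 and *b* = 0.1:

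- *m* = +1.0, *s* = 4.0: 0.1 × 5.66 / √1.16 = 0.53
- *m* = −1.8, *s* = 3.3: −0.18 × 5.66 / √1.109 = −0.97
- *m* = −3, *s* = 3 (illustrative): −0.3 × 5.66 / √1.09 = −1.63

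From the noncentral t distribution with 31 degrees of freedom, the false-positive rates at a nominal 5% are:

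| Enrolment | *b* = 0.05 | *b* = 0.1 | *b* = 0.2 |
|---|---|---|---|
| Mean 0 | 5% | 5% | 5% |
| +1.0 h, SD 4.0 | 6% | 8% | 14% |
| −1.8 h, SD 3.3 | 8% | 16% | 38% |
| −3 h, SD 3 | 13% | 35% | 80% |

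A 20,000-run simulation of the first and last rows agrees to within about one percentage point (13%, 35% and 81% for the last). In the same runs a between-arm t-test stayed at about 5% throughout.

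**COVID contrast.** Modelled day length at 52.4 N runs from 7.7 to 16.8 h. The difference in mean daylight between the groups could be anything from 0 to a bound of 16.8 − 7.7 = 9.1 h, depending on when each is recruited.

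**The case against.** The strongest reply is that the design already deals with season. Allocation is 1:1 with a concurrent control, so a between-arm test is unbiased. The bias in evaluating the programme arises because the analysis section names a paired test and no test between arms, which is a wider defect. Enrolment spread evenly over a full year leaves the paired test at 5%, and nothing shows that the two cohorts will be recruited in different months. Covariates for actigraphy measures are also often left to an analysis plan, and this is a condensed article.

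Most of this stands and limits the point. It does not remove it. The section does name specific tests, and a plan that adjusted for day length would have to depart from them. The intention-to-treat wording suggests that a comparison of arms is meant, but the only change test named is paired. Nothing in the document keeps enrolment even or aligns the cohorts in time.

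Four stronger readings might be inferred, and the document does not support them:

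- *That step counts are compromised.* The pedometer records steps daily throughout in both arms, so controls show the seasonal drift. Neither steps nor physical activity is a listed outcome.
- *That the randomised comparison is biased.* It loses only precision.
- *That the 4 h SD measures the error in the outcomes.* It is an input in hours of daylight; the response of each outcome is unknown.
- *That the primary outcome is affected.* Nothing here bears on left ventricular global longitudinal strain.

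**Conclusion.** The point holds for the accelerometer-based sleep-timing, circadian and light-exposure outcomes, and it is minor. The SD of about 4 h in day-length change is firm if the latitude is near 52.4 N and starts cover at least a year. The two biases are conditional: on enrolment uneven over the year for the paired tests, and on different recruitment months for the COVID contrast. With even coverage from January 2022 to June 2023 the inflation is modest (6% to 14% for the assumed slopes), and it grows as enrolment bunches. The slopes are assumptions, so neither the bias nor the loss of precision can be given as a single figure.

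**What to change.** In Data analysis methods, state that the accelerometer-based sleep-timing, circadian and light-exposure outcomes will be analysed with a linear model:

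- **Arm contrast:** compare the two randomised arms, with the baseline value and the change in day length between the two recording weeks as covariates. This replaces the paired test as the evaluation of the programme.
- **COVID versus non-COVID contrast:** adjust for day length in the baseline week.
- **Sleep timing:** keep local clock time. Converting to UTC would create an artificial 60-minute shift in anyone who keeps the same local bedtime across a clock change.

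Day length follows from the recording dates, so no new data or visits are needed. The cost is one or two degrees of freedom and an assumption that the effect of day length is linear. If the COVID and non-COVID groups hardly overlap in calendar time, the adjustment rests on that assumption, so recruiting both over the same months is the better protection.

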### Intervention

#### Physical activity intervention group

The exercise intervention group will undergo a 12-week home-based physical activity intervention. The participants will be asked to increase their daily steps by at least 2000 steps per day from baseline, e.g. walking for approximately 30 min in addition to baseline, 5 days a week. A large cohort study of 9306 participants demonstrated that an incremental increase in physical activity of 2000 steps per day reduced the risk of cardiovascular events by 10% [30]. A pedometer will be provided to all participants with a diary sheet to record the number of steps per day. Weekly telephone calls lasting 10–15 min each will be made to each participant in the intervention group to provide an opportunity for the participants to ask any questions and for the research staff to encourage the participant to achieve their step goal. Suitable days and times will be arranged for phone calls to take place. After the intervention period, i.e. 13 weeks from the date of the initial visit, participants will be invited to visit the laboratory for follow-up assessments. One week will be allowed for the participants to record their baseline step count. On the first day of the second week, researchers will contact the participant to inform them of which group they have been allocated to. The same outcomes will be measured during the follow-up visit to determine a value of change.

#### Control group

The control group will be provided with a pedometer to record daily step count but will not need to increase daily step count. Once the 12 weeks have been completed, participants will be invited to attend the research laboratory for follow-up assessments.

### Outcome measures

The primary outcome measure is mean change in left ventricular global longitudinal strain after 12 weeks of the study intervention. Secondary outcomes are mean changes from baseline to the end of the intervention period in arterial stiffness (pulse wave velocity and augmentation index), measures of systolic and diastolic function of the heart (i.e. left ventricular ejection fraction, cardiac output, stroke volume, cardiac power, early-to-late filing ratio, right ventricular global longitudinal strain, left atrial strain, ventricular-arterial coupling, right ventricular diastolic function), heart rate variability, functional capacity, lung function, inflammatory and cardiac biomarkers, quality of life and well-being (depression, anxiety, stress, fatigue and sleep measures). Sleep measures include bedtime (h:min), wake-up time (h:min), time-in-bed (h), total sleep time (h), sleep onset latency (min), sleep efficiency (%), number of awakenings and wake after sleep onset (WASO, min), number and timing of naps, inter-daily variability and stability (as markers of circadian rhythmicity), and timing and nature of light exposure during a 24-h period. Additionally, we will assess the differences in the COVID-19 group vs. the non-COVID-19 group.

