### Sample size

One hundred twenty participants aged between 50 and 85 years will be recruited for the study. This will include 80 participants with a history of COVID-19 and 40 healthy individuals without a history of COVID-19 to complete baseline assessments. Additionally, participants with a history of COVID-19 will be randomly assigned (1:1) to either a 12-week home-based physical activity intervention or usual care control group. The study design is outlined in Fig. 2. The primary outcome measure is LV GLS, as a measure of cardiac systolic function. With a type I error of 0.05 and an intended high power of > 90%, 40 participants per group are required to detect a 3% difference in LV GLS between the COVID-19 and non-COVID groups. In response to the physical activity intervention within the COVID-19 group, assuming a standard deviation of 2.5% and an estimated attrition rate of ~ 20% in the intervention period of the study, 40 participants per group will be required, providing the overall recruitment target of 80 participants with a history of COVID-19.

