### Randomisation

Randomisation numbers will be generated by secure web-based randomisation to maintain concealment and minimise selection bias. The randomisation process will be performed by the researchers, and the principal investigator will generate the randomisation numbers. A randomisation sequence was computer generated, with each allocation assigned a number. Following baseline testing, each participant was asked to pick out a number from an opaque box. Participants were blinded to their allocation to ensure a ‘usual’ baseline week was obtained; however, due to the nature of the intervention, researchers (i.e. outcome assessors and analysts) were unblinded to the allocation.

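### Pre-randomisation LV GLS enters the plan only by subtraction; a baseline-adjusted comparison of the randomised arms would be more precise at almost no cost

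*Protocol article*

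**What the plan says.** The Outcome measures section fixes the primary outcome as a change score: "The primary outcome measure is mean change in left ventricular global longitudinal strain after 12 weeks of the study intervention". The secondary outcomes there are likewise defined as mean changes over the intervention period. The section on the physical activity intervention group describes the follow-up visit in the same way: "The same outcomes will be measured during the follow-up visit to determine a value of change".

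Baseline LV GLS is known before allocation. The Randomisation section says: "Following baseline testing, each participant was asked to pick out a number from an opaque box". No stratification factor is mentioned.

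The Data analysis methods section names three kinds of test:
- an independent-samples t-test or Mann–Whitney test, which "as appropriate, will be used to assess the differences in variables between COVID and non-COVID groups";
- a paired t-test or Wilcoxon signed-rank test, which "will be used to evaluate the differences in variables pre- and post-intervention";
- Pearson or Spearman correlations.

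None of these takes a covariate. No regression, ANCOVA or mixed model is named, and no test is assigned to intervention versus control. The analysis uses complete cases only.

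**The concern.** Subtracting baseline from follow-up fixes the baseline coefficient at 1. With equal variances at the two visits, the coefficient that minimises the variance of the arm contrast is rho, which is below 1. A change-score contrast therefore over-corrects for a chance difference between the arms at baseline. The arm that happens to start with worse strain tends to show the larger improvement through regression to the mean, and this can imitate an exercise effect or mask one.

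At stake is the precision of the primary randomised comparison in a trial that expects about 32 completers per arm. The continuous secondary outcomes are defined in the same way, and their correlations between visits will differ, so rho cannot be presumed high for all of them.

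**Working it through.** **Inputs from the article (Sample size section).** There are 40 randomised per arm with about 20% attrition, so 40 × 0.8 = 32 completers per arm. Alpha is 0.05, taken here as two-sided. The SD is 2.5%, without saying whether it belongs to a single measurement or to a change. The only stated difference is for another contrast: "40 participants per group are required to detect a 3% difference in LV GLS between the COVID-19 and non-COVID groups". No difference is given for intervention versus control.

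**Assumed.** Rho is not in the article; 0.3 to 0.9 is used as a range. Variances at the two visits are taken as equal.

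**The plan's own figure.** Taking 3 points and SD 2.5 at two-sided 0.05 and 90% power, n = 2 × (1.960 + 1.282)² × 2.5² / 3² = 14.6, so 15 per group, or 15/0.8 = 18.75, so 19 after attrition. The stated 40 is not reproduced. That is a separate matter, but it shows that the article's inputs do not fix the arm effect the trial is meant to detect.

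**Precision.** Let s be the SD of a single measurement.
- Change score: variance per participant 2(1 − rho)s²
- Baseline-adjusted: (1 − rho²)s²
- Ratio, adjusted to change score: (1 + rho)/2

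At rho 0.5 the ratio is 0.75, so a change-score analysis would need 32/0.75 = 42.7, about 43 completers per arm, to match 32 with adjustment.

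**Power if 2.5 is the SD of change.** Noncentral t, 32 per arm, 62 df for the change score and 61 df adjusted, adjusted SD = 2.5 × √((1+rho)/2). The change score has 80% power at 1.78 points and 90% at 2.06 points.

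| rho | variance ratio | adjusted SD | adjusted power at 2.06 points |
|---|---|---|---|
| 0.3 | 0.65 | 2.02 | 98.0% |
| 0.5 | 0.75 | 2.17 | 96.3% |
| 0.7 | 0.85 | 2.30 | 94.0% |
| 0.9 | 0.95 | 2.44 | 91.4% |

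At 1.78 points, 80% becomes 93.5%, 89.9% and 85.9% at rho 0.3, 0.5 and 0.7. At 3 points the change score already has 99.7% power.

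**Power if 2.5 is the SD of a single measurement.** The SD of change is then 2.5 × √(2(1−rho)) and the adjusted SD is 2.5 × √(1−rho²). At 2.06 points:

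| rho | change score | adjusted |
|---|---|---|
| 0.3 | 78.3% | 92.5% |
| 0.6 | 95.2% | 98.2% |
| 0.7 | 98.7% | 99.5% |
| 0.8 | 99.9% | about 100% |

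At rho 0.5 the SD of change is 2.5 × √1 = 2.5, so the two readings coincide there.

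**Chance imbalance.** For a baseline arm difference d, the change-score contrast is shifted by −(1 − rho)d. If 2.5 is the single-measurement SD, d has SD 2.5 × √(2/32) = 0.625 points. At rho 0.5 a 1-SD imbalance shifts the contrast by 0.5 × 0.625 = 0.31 points in the opposite direction, about 15% of 2.06.

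This is the same loss seen from another side. The change-score variance minus the adjusted variance is [2(1 − rho) − (1 − rho²)]s² = (1 − rho)²s². At rho 0.5 that is 6.25 − 4.6875 = 1.5625 = 0.25 × 6.25. Multiplied by 2/n, it is exactly the variance of the imbalance shift.

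**The case against.** The strongest reply is that the article never states the analysis being criticised. It assigns the independent-samples test to COVID versus non-COVID and the paired test to pre versus post, and it assigns nothing to the randomised arms. A change outcome is also compatible with adjustment, since a model of change on arm plus baseline gives the same arm effect as a model of the follow-up value. Covariates are often left to an analysis plan, and none is shown here. On this view the real gap is the missing between-arm test, and adjustment is only part of filling it.

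Much of that stands. A reader might infer that the protocol commits to an unadjusted two-sample test of change between the arms. It does not; that test is a reading of the outcome definition. Not stratifying on baseline strain is no error either. The size of the gain also rests on quantities the article omits, and the 1.78 and 2.06 point differences were chosen to give round power for the change score.

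Deferral to an unseen plan does not dispose of the point. The article does not leave its methods open. It lists the tests, all of them covariate-free, and fixes the outcome as a change. Followed as written, it cannot give a baseline-adjusted estimate. Repairing the missing comparison in the most obvious way, with a t-test on change scores, would keep the loss.

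**Conclusion.** The point holds as one of efficiency. The plan uses baseline LV GLS only by subtraction, and a change-score comparison of the arms would be less precise than an adjusted one for any rho below 1, apart from the one degree of freedom.

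The size is uncertain. With 32 completers per arm and 2.5 as the SD of change, 90% power rises by between 1.4 points (rho 0.9) and 8.0 points (rho 0.3). With 2.5 as the single-measurement SD and a 2.06-point difference, the gain runs from about 14 points (rho 0.3) to almost none (rho 0.8). If the true arm difference is near 3 points it is negligible, but the article states 3% only for COVID versus non-COVID.

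Three stronger conclusions may tempt a reader and are not supported:
- **That the change-score estimate is biased.** It is unbiased over repeated randomisations.
- **That it carries a baseline imbalance in full.** Only the fraction (1 − rho) remains, with reversed sign.
- **That lost precision and residual imbalance are two harms.** They are one.

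Nor does this show that the trial is underpowered, because no arm effect size is stated against which to judge it. A change is recommended because it costs so little, not because the plan is invalid without it.

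**What to change.** In Data analysis methods, state the primary randomised comparison as a linear model of follow-up LV GLS (or of its change, which gives the same arm effect) on arm, with baseline LV GLS as covariate. Report the adjusted mean difference with its 95% CI. Use the same form for continuous secondary outcomes measured at both visits. Mean change per arm can stay as a descriptive summary.

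This also supplies the between-arm analysis that the section lacks. Because the Randomisation section says analysts are not blinded, fixing the model in advance also removes a later choice between adjusted and unadjusted results.

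The cost is wording and one degree of freedom. The baseline values are already collected, the named software fits the model, and no further participants or procedures are needed.
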